### Outcomes {12}

All participants will undergo assessment by the research team pre-operatively, and at 6 weeks, 6 months, 12 months and 24 months post-operatively. The research team will assist in the randomisation process and cannot be blinded to the allocation. The FJS, OKS, IKSS, KOOS, EQ-5D-5L, Net Promoter, BPI, PSQ and VAS pain are all validated clinical assessments of patients undergoing TKA [10, 32–38]. Physiotherapists will also record functional measures of recovery during in-patient stay and will be blinded to the allocated alignment. The functional measures were selected from recommended list as described by Dobson et al. [39] and include: 4 X 10 m walk test, passive and active range of motion, 30-s sit-to-stand test and a 3-step stair ascend and descend test. A breakdown of outcome measures is displayed in Table 1.

**Table 1 Tab1:** Participant evaluation schedule

Evaluation	History/pre-op	Intra-op	In-patients	6 weeks	6 months	12 months	24 months
Demographics	X						
Medical history	X						
CT scan	X						
Surgical details		X					
Physiotherapy functional tests			X	X			
Recovery				X			
BPI	X		X	X			
PSQ	X						
Satisfaction					X	X	X
Net promoter					X	X	X
OKS	X			X	X	X	X
IKSS	X						X
FJS-12				X	X	X	X
KOOS	X						X
EQ-5D-5L	X			X	X	X	X
VAS pain	X			X	X	X	X
AP and ML X-ray	X						X
Long leg X-rays	X					X	

### Participant timeline {13}

Participants will be recruited from North Shore Hospital, Auckland and the Elective Surgery Centre, Auckland. Based on other randomised control trials performed at this site [40], this trial aims to recruit 12 patients per month. The recruitment process is estimated to take 22 months and began in November 2020. Results are anticipated in December 2025.

### Sample size {14}

This trial seeks to determine if robotic arm-assisted TKA following FA principles provides superior clinical outcomes to robotic arm-assisted TKA following MA principles. Ingelsrud et al. [41] reported that the minimal clinically important change in FJS for TKA patients was 14 points. As there is limited published literature on FA performed with robotic arm-assistance, the power calculations have assumed an effect size of 14, which represents a measure of superiority. A standard deviation of 26 is estimated using the Spearman correlation of 0.61 between the anchor score and change score from patients classified as ‘somewhat better’, which is also taken as a measure of superiority. Using a power of 80% (*β* = 0.2), significance level of 5% (*α* = 0.05) and accounting for 10% loss to follow-up yields a sample size of 120 participants per arm.

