### Trial design {8}

This study is a prospective, singe-centre, single blinded, randomised controlled trial, where 240 patients will be allocated to robotic arm-assisted TKA following either MA (control group) or FA (intervention group). Participants will be randomly allocated in blocks of four following their eligibility assessment and provision of consent. The study seeks to assess if the interventional surgical technique is superior to the control, where superiority is defined as a patient reported outcome that meets the minimum clinically important difference (MCID) and patient acceptable symptom state (PASS) at 2 years.

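### The stated inputs (difference 14, SD 26, 80% power, 5% alpha, 10% loss) require about 62 patients per arm, about 120 in the whole trial, not 120 per arm

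*Protocol article*

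**What the plan says.** The calculation is in the protocol article, Sample size {14}. On the target difference it says "the power calculations have assumed an effect size of 14, which represents a measure of superiority". On variability it says "A standard deviation of 26 is estimated using the Spearman correlation of 0.61 between the anchor score and change score", where the patients concerned are those in the 'somewhat better' anchor category of the cited study. It then sets power at 80% and alpha at 0.05 and concludes that "accounting for 10% loss to follow-up yields a sample size of 120 participants per arm".

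Trial design {8} carries the doubled figure forward: "where 240 patients will be allocated to robotic arm-assisted TKA". The Abstract also gives 240. The per-arm label is therefore used consistently and is not an isolated slip. The primary outcome, in the Abstract and in Objectives {7}, is the FJS at 2 years.

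**The concern.** Every input needed for a two-sample calculation is printed beside the result, so the result can be checked, and it is about twice what the inputs produce. Either the sample size is not what the stated criterion requires, or one of the inputs is not the one used.

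The 80% power is then a property the design does not have on its own assumptions. The stated rationale supports randomising about half the surgical patients planned. A reader who takes 80% power at 14 points at face value will misjudge how sensitive the trial is: on the stated SD, an observed difference of about half the 14-point target would already be statistically significant.

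The SD adds to the problem. A correlation has no units and cannot by itself yield an SD in FJS points. The quantity described is a change score in one anchor category, whereas the trial compares the 2-year FJS of all patients. Table 1 schedules no pre-operative FJS, so this trial cannot form a change from before surgery. The SD matters because it decides which repair is right.

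**Working it through.** **Inputs, all from Sample size {14}:** difference δ = 14; SD σ = 26; power 80%; α = 0.05; loss 10%. Sidedness is not stated, so two-sided is assumed. Allocation is taken as 1:1, as 120 in each arm implies.

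**Attempt to reproduce 120 per arm**

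n per arm = 2 × (z₀.₉₇₅ + z₀.₈₀)² × σ² / δ²

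= 2 × (1.960 + 0.842)² × 26² / 14² = 2 × 7.849 × 676 / 196 = 54.1, rounded up to 55. The t-test needs 56.

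Allowing for 10% loss: 55 / 0.9 = 61.1, so 62 per arm (124 in total). By the t-test, 56 / 0.9 = 62.2, so 63 per arm (126 in total). Multiplying by 1.10 instead of dividing by 0.9 gives 61 per arm (122 in total).

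The stated 120 per arm is not reproduced. It does match the unrounded total for both arms: 2 × 54.14 = 108.3, and 108.3 / 0.9 = 120.3.

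**Variants tried, enrolled after 10% loss**

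| Variant | Result |
|---|---|
| One-sided 5% | 48 per arm |
| Rank test, efficiency 0.955 | 65 per arm |
| Rank test, efficiency 0.864 | 72 per arm |
| Bonferroni for 12 tests | 106 per arm |
| SD rescaled in several ways using 0.61 | 38, 48, 97 or 163 per arm |
| 4:1 allocation | 189 in total |

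None gives 120 per arm.

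**What would give 120 per arm**

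Multiplying the SD by √2 gives 26 × 1.414 = 36.8. The formula then needs 109 evaluable per arm, and 109 × 1.10 = 120 (109 / 0.9 gives 122). That would count the two-arm variance twice, and the protocol states no such step. With SD 26 kept, about 120 per arm also follows from a target difference near 10 points or from power near 97.5%. Neither is stated.

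**What 120 per arm delivers**

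Evaluable per arm: 120 × 0.9 = 108. Standard error of the difference at SD 26: 26 × √(2/108) = 3.54.

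- Power for 14 points (noncentral t): 97.6%.
- Difference detectable with 80% power: 10.0 points; with 90% power: 11.5 points.
- Smallest observed difference significant at two-sided 5%: 1.97 × 3.54 = 7.0 points.

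Power for 14 points with 108 evaluable per arm, by SD:

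| SD | Power |
|---|---|
| 26 | 97.6% |
| 30 | 92.7% |
| 32 | 89.3% |
| 36.8 | 79.5% |

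**The case against.** The strongest reply is that, on the stated inputs, the error makes the trial larger than needed. It does not bias the comparison or inflate its type I error, and a null result from a larger trial is more informative. That is correct, and the point should not be read as a threat to the validity of the primary test.

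Trial design {8} also ties superiority to reaching the minimum clinically important difference (MCID) and the patient acceptable symptom state (PASS), and Statistical methods {20a} assesses clinical significance against both. A significant 7-point difference would therefore not by itself count as superiority under the protocol's definition. This limits the harm from a small significant result but does not make the power statement true.

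The cause cannot be read from the text. A total may have been labelled per arm, the variance doubled, or a different SD, difference or power used. If an input was misreported, 240 may be the intended number. This stands, and the correction has to allow for it. The match with 120.3 is suggestive but not proof, since rounding up gives 122 to 126.

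The 97.6% is conditional on an SD whose basis is itself in doubt, and on 1:1 allocation. The Abstract speaks of a 4:1 ratio; a literal 4:1 split of 240 with 10% loss would have about 88% power. That still does not reproduce 80%, and it contradicts equal arms of 120.

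Finally, the cited study is not at hand and may contain further figures from which an SD could be derived. What can be said is that the derivation as written does not produce one.

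**Conclusion.** The concern holds. The inputs in Sample size {14} yield 62 to 63 enrolled patients per arm, about half the stated 120, and no adjustment given in the protocol closes the gap. With 108 evaluable per arm, SD 26, 1:1 allocation and a two-sided 5% test, power for 14 points is 97.6%, and the difference detectable with 80% power is 10.0 points. If the other inputs are held fixed, only an SD of about 36.6 to 36.8 makes 120 per arm and 80% power consistent.

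This is not a matter of condensation in a journal article: the inputs and the result are both printed, and they contradict each other. It must be corrected because it is the stated justification for the size of the trial. Which figure is wrong is for the sponsor to establish.

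**What to change.** Reconcile the paragraph in Sample size {14} with 120 per arm, in one of two ways.

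1. If SD 26 was intended, keep 240 if wished and state what it provides: 120 per arm (108 evaluable) gives 97.6% power for a 14-point difference, or 80% power for a 10-point difference, at SD 26 and two-sided 5%.
2. If a larger SD, near 36.8, or another difference or power was used, state it and give its source.

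In either case, remove the derivation of the SD from the correlation. Justify the SD as that of the 24-month FJS across all patients, show power over a range such as 26 to 36.8, and state that the test is two-sided.

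The cost is wording only. No further patients are needed, but the sponsor has to acknowledge that the figure was mis-stated.

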### Recruitment {15}

This trial includes five high volume arthroplasty surgeons from a large public teaching institution in Auckland. The orthopaedic consultant surgeons and research team will screen potential participants from the hospital waitlist. Participants that meet the eligibility criteria and express interest in participating will be provided with a patient information sheet. The research team will then telephone potential participants to confirm if they would like to enrol in the study. Patients were recruited face-to-face at a radiology appointment and will be recruited remotely during COVID-19 lockdowns.

### Assignment of interventions: allocation

#### Sequence generation {16a}

Participants will be recruited in a block size of 4:1, which aims to maintain balanced treatment arms over time. A master randomisation sequence will be generated prior to the start of the trial using an online random number generator (www.sealedenvelope.com). The master sequence will be maintained by the sponsor and patients will be allocated a treatment in sequential order following consent. The study team and surgeon will be notified of allocation prior to surgery.

#### Concealment mechanism {16b}

The sponsor will maintain the master randomisation sequence and will email the allocation treatment to the research team as each patient provides consent to participate in the trial.

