### Who will take informed consent? {26a}

Informed consent will be obtained by either the orthopaedic consultant surgeon or the research coordinator, both of whom are trained in the study requirements and will be appropriately onboarded. Consent will be collected at the pre-operative radiology visit which is scheduled up to 6 months before surgery, but normally occurs within 4 weeks of admission. Māori cultural support is also available as per the New Zealand ethics guidelines.

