#### Implementation {16c}

The research team will email the sponsor with the unique de-identified patient study number once a patient has been enrolled. The research team will inform the Investigating surgeons of the randomised intervention one day prior to surgery.

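### Blocks of four on one list, with each allocation emailed around consent to the team that recruits, could let that team deduce up to a third of allocations beforehand

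*Protocol article*

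**What the plan says.** All references are to the protocol article.

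- **Block size.** Trial design {8}: "Participants will be randomly allocated in blocks of four following their eligibility assessment and provision of consent". No other size is given and no stratification is described. Sequence generation {16a} words it differently: "Participants will be recruited in a block size of 4:1, which aims to maintain balanced treatment arms over time".
- **List.** Sequence generation {16a} describes one master sequence, made before the trial starts, held by the sponsor and used in order after consent. The trial has one centre.
- **Release to the research team.** Concealment mechanism {16b}: the sponsor "will email the allocation treatment to the research team as each patient provides consent to participate in the trial". Under Implementation {16c} the team emails the sponsor once a patient is enrolled.
- **Release to surgeons.** Implementation {16c}: "The research team will inform the Investigating surgeons of the randomised intervention one day prior to surgery". Strategies to improve adherence {11c} gives the same day.
- **Who recruits.** Recruitment {15}: "The orthopaedic consultant surgeons and research team will screen potential participants from the hospital waitlist"; the research team then telephones candidates. Under {26a} either the surgeon or the research coordinator takes consent. Who will be blinded {17a} says the research team is not blinded.
- **Timing.** {26a}: "Consent will be collected at the pre-operative radiology visit which is scheduled up to 6 months before surgery". The same sentence adds that it normally takes place within 4 weeks of admission.
- **Ratio.** Sample size {14} "yields a sample size of 120 participants per arm", that is 1:1 for 240 patients. The Abstract gives 4:1.

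**The concern.** Sponsor custody of the list hides the next entry from direct view. It does not stop someone who has seen every earlier entry from working the next one out, and in a block of four the last entry always follows from the first three. Here the running record of allocations goes to the people who recruit, and the block size is printed in the protocol that investigators must sign off.

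If staff can tell which arm the next consenting patient will receive, they can bring a consent visit forward, defer it, or lean on a judgement. Eligibility criteria {10} leave room for judgement: suitability for a cruciate-retaining implant, indication for robotic surgery, and willingness and ability to comply. Patient blinding acts after this point and does not repair it. Baseline adjustment is a weak safeguard for the primary outcome, because Table 1 schedules no pre-operative Forgotten Joint Score. The Discussion nevertheless relies on the blinded randomisation for low bias.

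**Working it through.** The protocol states no predictability figure, so there is none to reproduce.

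**Inputs.** Block size 4 (Trial design {8}). Ratio 1:1, inferred from 120 per arm (Sample size {14}) and from the aim of balanced arms ({16a}). Total 240. Recruitment 12 a month (Participant timeline {13}). Consent normally within 4 weeks of admission ({26a}).

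**Step 1: share known with certainty.** A 2:2 block has 6 equally likely orders. AABB and BBAA each fix positions 3 and 4, giving 2 certain entries each. The other four orders fix only position 4, giving 1 each.

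(2 × 2 + 4 × 1) / (6 × 4) = 8/24 = 33.3%, and 240 × 1/3 = 80 patients expected.

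**Step 2: best guess.** The chance of a correct guess at positions 1 to 4 is 1/2, 2/3, 2/3 and 1.

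(1/2 + 2/3 + 2/3 + 1) / 4 = 17/24 = 70.8%, against 50%.

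**Step 3: how far this depends on prompt emails.** Suppose the last *h* allocations are still unseen when the next patient consents. At position *p* the observer then knows max(0, *p* − 1 − *h*) entries of the current block.

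| *h* | Certain | Best guess |
|---|---|---|
| 0 | 8/24 = 33.3% | 17/24 = 70.8% |
| 1 | 1/4 × 1/3 = 1/12 = 8.3% | (1/2 + 1/2 + 2/3 + 2/3)/4 = 58.3% |
| 2 | 0 | (3 × 1/2 + 2/3)/4 = 54.2% |
| 3 or more | 0 | 50% |

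For *h* = 1, position 4 is certain only if the first two entries match (probability 1/3). The one-third is therefore a ceiling, reached when each email arrives before the next consent.

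**Step 4: the other reading of the ratio.** If 4:1 were literal, in blocks of five, 11 of 25 entries (44%) would be certain. That reading does not remove the problem, and it is incompatible with 120 per arm.

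**Step 5: effect of later release.** Twelve consents a month is about 3 a week (12/4). If release waits until the day before surgery, the number hidden at any consent is about 3 × weeks from consent to surgery: 3 at 1 week, 6 at 2 weeks, 12 at 4 weeks. With 52/12 = 4.33 weeks to a month these become 2.8, 5.5 and 11.1. By Step 3, three hidden entries already cover the current block if surgery follows consent order. The protocol does not say that it does, so a longer lag gives useful margin.

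**Step 6: effect of varied block sizes alone.** This was simulated with 1,000 lists of 240 and an observer who knows the set of sizes but not the draw.

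| Sizes | Certain | Best guess |
|---|---|---|
| 4 only | 33.3% | 70.8% |
| 4, 6 | 5.5% | 69.3% |
| 4, 6, 8 | 2.2% | 68.0% |

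Varying the size removes most of the certainty but little of the guessing advantage.

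**The case against.** The strongest reply is that the protocol has real safeguards. The sponsor holds the list, nobody at the site sees the next entry directly, allocation follows consent, and surgeons are not told until the day before surgery. These points stand and they narrow the finding. They do not answer it, because the deduction uses earlier entries that the research team does hold.

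Several stronger readings are tempting and are not supported:

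- *A third of allocations are known.* This needs fixed 1:1 blocks and prompt emails. That the size is fixed is inferred from the single size given, and no email turnaround is stated. {16a} says only that the team and surgeon are notified before surgery.
- *The team has foreknowledge at screening.* Slots follow consent order, and others may consent between a telephone call and the radiology visit. Usable foreknowledge arises mainly at the consent visit.
- *Surgeons can predict the next arm.* They learn allocations later, so their knowledge lags unless the team shares it.
- *Allocations are typically out for six months before surgery.* That is the outer limit; the normal interval is within 4 weeks.
- *Early release biases baseline questionnaires or creates post-randomisation losses.* The questionnaires are completed by blinded patients, mostly electronically. The slot is assigned at consent whenever the email is sent, so ordinary cancellations would still follow randomisation.

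**Conclusion.** The point holds as an avoidable weakness in concealment. Under blocks fixed at four, a 1:1 ratio and prompt emails, the research team could deduce up to 33.3% of allocations with certainty (80 of 240 expected) and guess correctly up to 70.8% of the time. A single unseen allocation at each consent would lower these to 8.3% and 58.3%, so the true exposure depends on a turnaround that the protocol does not give. A reader might infer that selective enrolment took place; nothing in the document shows that. The 4:1 wording in the Abstract and in {16a} contradicts 120 per arm and has to be reconciled whichever figure is used. The change is worth making because the protocol gives no reason for the research team to hold allocations earlier than the day already set for telling surgeons.

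**What to change.** For patients not yet allocated:

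1. Amend Sequence generation {16a}, Concealment mechanism {16b} and Implementation {16c} so that the sponsor releases each allocation only on the day before surgery, when the surgeon is told. This is the main remedy.
2. Generate the rest of the list with randomly varied block sizes, such as 4, 6 and 8, and keep the sizes out of documents held at the site. The size of four is already published, so only new, undisclosed sizes help. This step is secondary.
3. State the allocation ratio once and correct the conflicting 4:1 wording in the Abstract and {16a}.

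For patients already allocated, report the release mechanism as a limitation and examine baseline balance between arms. Trial status puts the end of recruitment at June 2022. If no patients remain to be allocated, this reporting and the correction of the ratio are all that can be done.

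The cost is a later email, a regenerated remainder of the list, less scheduling notice for the research team, and slightly less exact balance at the interim analyses.

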#### Implementation {16c}

The research team will email the sponsor with the unique de-identified patient study number once a patient has been enrolled. The research team will inform the Investigating surgeons of the randomised intervention one day prior to surgery.

### Assignment of interventions: blinding

#### Who will be blinded {17a}

The participants and physiotherapists will be blinded to the treatment allocation. All participants will be assigned a unique study number following a consecutive order of consent. The participant identification list will be archived at the site on a secure network in a password-protected file. The investigators and research team are unable to be blinded to the allocation due to their role in the allocation of treatment and execution of surgery.

#### Procedure for unblinding if needed {17b}

Participants will be unblinded to the intervention at the end of the trial, unless there is a medical reason to do so prior to the end of the study.

### Data collection and management

#### Plans for assessment and collection of outcomes {18a}

Outcomes will be primarily captured and stored using a password-protected electronic platform (OBERD, Columbia, MO, USA). Participants will be sent automatic email reminders to complete their questionnaires. In the instance of non-compliance, the study coordinators will provide paper case report forms. The physiotherapists are also provided with an instruction manual and equipment to standardise the functional measures, which are collected on paper case report forms.

#### Plans to promote participant retention and complete follow-up {18b}

Electronic data capture will provide participants with the flexibility to complete the case report forms at their own convenience. Travel compensation for non-standard of care visits such as radiology appointments will also be provided to ensure retention is maintained. Participants who are classified as *intent to treat* but do not meet the surgical criteria will continue to be followed-up for outcome and safety purposes.

#### Data management {19}

The International Council for Harmonisation guidelines for Good Clinical Practice (ICH GCP) will be followed throughout the study. The sponsor will conduct routine monitoring visits for data verification against source material, as defined by participant entered data or medical records. Data collected by the sponsor will be stored electronically in a password-protected folder with restricted user access. Periodic surgeon investigator meetings will also be held to review participants where treatment has deviated from the protocol. The chief investigator will be responsible for the training and sign-off of all staff working on the study.

